### Phase III: Implementation of the community-based model of care

In this phase, the multi-packaged model of care co-developed in Phase II will be put in to action to enhance access to and utilization of health services for hypertension and diabetes mellitus screening, and initiation of treatment for those diagnosed among CALD communities in Brisbane city, Australia. This phase will be guided by the preparation and implementation components of EPIS Framework and the consolidated framework for implementation research (CFIR). The preparation component of EPIS will be utilized to guide the process of getting readiness for implementation. This includes developing training manuals and implementation evaluation checklists, building staff capacity through training, collaborating with implementing sites in developing infrastructure to support the practice, and carefully planning the implementation of the care model to fit the local context while maintaining fidelity. In addition, putting clear mechanisms to proactively identify potential barriers and strategize ways to address them will be part of preparation to ensure that the implementing organizations are well-positioned for successful execution. Baseline data collection will also be conducted at this time as part of the quasi-experimental study of the implementation process pilot testing.

Once the pre-implementation preparation phase is completed, the actual model implementation phase will be started in the selected faith-based community settings in collaboration with different health care providers in the city. These collaborating health facilities will be tasked to work with the faith-based CALD community leaders on ways of enhancing access to and utilization of health services for hypertension and diabetes mellitus screening, and initiation of treatment for those diagnosed. For the pilot testing purpose, the implementation process will focus on involving adults aged 40 years and above. Accordingly, we will be communicating with those religious organizations for their consent and cooperation once the ethical approval process is finalized and permissions are obtained from other concerned bodies in the health system. Then, people from these communities who were born overseas and are 40 years or older will be registered and invited for the service in collaboration with the project implementing health facilities. Additional key activities in this phase includes executing the plan, monitoring fidelity and outcomes through data collection, and using feedback for continuous improvement. Essential support systems such as coaching, supervision, and resource provision will be facilitated by the project advisory group in collaboration with the implementing site managers/coordinators during this phase, to sustain momentum and address challenges. Flexibility and responsiveness to real-time feedback will be emphasized to ensure that the multi-packaged interventions are delivered effectively, and adjustments are made when needed.

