### Outcomes of model implementation

The primary model implementation impact outcome is “Reach”, or the proportion of eligible CALD adults completing hypertension and/or diabetes screening. The primary implementation process outcomes are acceptability, appropriateness, and feasibility of the model of care, measured at the site and stakeholder level. Secondary outcomes include follow-up completion, treatment initiation, clinical control (BP and glycemia), intervention fidelity, program cost, and sustainability. Baseline measurements will be collected prior to implementation, with follow-up assessments occurring at 6 to 12 months post-implementation depending on the specific outcome (See Supplementary File 1). The sustainment component of EPIS framework and the RE-AIM evaluation framework will be utilized to guide assessment of these implementation outcomes related with implementation of the multi-packaged model of care. The RE-AIM framework is a widely used planning and evaluation tool in public health that helps assess the impact and scalability of health interventions across five key dimensions: Reach (the extent to which the target population participates), Effectiveness (the impact on important outcomes), Adoption (the extent to which settings and staff adopt the intervention), Implementation (how well the intervention is delivered as intended), and Maintenance (the extent to which a program is sustained over time) [35]. Originally developed to bridge the gap between research and real-world application, RE-AIM guides both the design and evaluation of programs to ensure they are not only effective in controlled trials but also practical and sustainable in everyday settings. However, some of the implementation outcomes in this study, specifically acceptability, appropriateness, feasibility, fidelity and cost are not native RE-AIM domains. These outcomes are intentionally drawn from Proctor et al.’s taxonomy to complement RE‑AIM’s implementation dimension with complementary measures being mapped pragmatically across the two frameworks [35, 36]. Reach will be calculated as the number screened divided by the number invited within each site and period based on community registries and screening logs. In addition, individuals who screen positive during each measurement period will form a nested cohort for follow up, and these clinical pathway outcomes will be summarised and analysed as site period proportions to remain consistent with the repeated cross-sectional design.

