
### Proposed tools for measuring implementation outcomes

There are various tools that have been utilized to assess various implementation outcomes across the literature. We will be using different adapted tools including the Acceptability of Intervention Measure (AIM), Intervention Appropriateness Measure (IAM), and Feasibility of Intervention Measure (FIM), psychometrically validated tools developed to assess key early-stage implementation outcomes. Each of these instruments consist of four items, rated on a five-point Likert scale from “completely disagree” to “completely agree.” The AIM captures the degree to which stakeholders find an intervention agreeable or satisfactory, making it a useful measure of perceived acceptability. The IAM evaluates whether an intervention is perceived as a good fit or relevant for a given context or problem, thereby assessing its appropriateness. The FIM measures the perceived practicality and ease with which an intervention can be successfully implemented in a specific setting. These tools are designed for ease of use, brevity, and reliability, making them highly suitable for integration into implementation research and practice across diverse settings [37]. In addition, other tools will be utilized depending on the expected outcome measures including the Clinical Sustainability Assessment Tool (CSAT), Short Form, and the Program Sustainability Assessment Tool (PSAT), Short Form, for model implementation sustainability assessment (Table 2).

**Table 2 Tab2:** Implementation outcomes and proposed assessment tools for the model of care

	Constructs	Assessment tools/Measures	Source of data	Method
RE‑AIM Implementation Evaluation Framework with Proctor et al. style implementation outcomes	Reach	Participation rate: % of individuals invited who actually undergo screening for the target NCDs.	Registry lists and clinical records	-
	Effectiveness	Follow-up rate: % of screen-positive individuals who receive timely confirmatory diagnosis and/or treatment.	Clinical records	-
		Proportion of people with controlled hypertension and diabetes among those diagnosed.	Clinical records	-
				-
	Adoption	Proportion of implementing agents/staffs that deliver model of care components.	Clinical records	-
	Implementation			
	✓ Acceptability	Acceptability of Intervention Measure (AIM) 4-items [37].	Implementing site staff members	Survey

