With regards to the sample size for this quasi-experimental study using the Difference-in-Differences approach, we have considered a hypertension prevalence of 34%, and an assumed baseline screening rate of 50% based on previous literature which shows that only one in two people detected to have hypertension are aware of their condition among the Australian population [4, 5]. Our target is to increase hypertension screening rates among CALD communities from 50% at baseline to at least 70% post-intervention, representing a 20% increase. To detect this difference with 80% power and a 5% significance level, we first calculated the sample size for comparing two independent proportions, assuming individual randomization. This yielded an unadjusted sample size of approximately 182 participants (91 per group).

Nevertheless, given the study’s clustered design involving 12 sites (six intervention and six control clusters), it is necessary to adjust for the expected intra-cluster correlation (ICC), which accounts for the similarity of responses within clusters. This adjustment is done by applying a design effect, calculated as: Design Effect (DE) = 1 + (m − 1) × ICC, where “m” is the average number of participants per cluster. In this study, we expect to recruit 100 participants per cluster and assume an ICC of 0.02 [41]. Applying these values, the design effect becomes: DE = 1 + (100 − 1) × 0.02 = 1 + 99 × 0.02 = 2.98. Applying this yielded an adjusted total sample size of approximately 543 participants, or about 272 per arm. Therefore, with the 100 expected participants from each cluster, the final planned sample size of 1,200 exceeds the minimum requirement and ensures sufficient power to detect the expected effect while remaining practical. Furthermore, the qualitative component will also include in-depth interviews, and stakeholder workshops with CALD communities, healthcare providers, and policymakers to explore perceptions, implementation processes, barriers, and enablers.

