### Data analysis plan for the main model

The Difference in Differences approach will be used to compare changes in hypertension and diabetes screening uptake between intervention and control sites over time with a repeated cross-sectional design. A Generalized Estimating Equations model will be utilized as the primary analysis method with site clustered robust standard errors and an appropriate small sample correction to account for the limited number of clusters. In addition, a generalized linear mixed model with a site level random intercept will be used as a sensitivity analysis. Key participant characteristics including age, sex, region of birth, education, primary language, and baseline comorbidities will be included as covariates. Results will be presented as adjusted marginal effects with 95% confidence intervals. Baseline equivalence between intervention and control sites will be examined using standardized mean differences, and any identified imbalances will be controlled for in the modelling. The parallel trends assumption will be assessed indirectly through these baseline comparisons and sensitivity analyses as only one pre intervention time point is available. For secondary outcomes, follow up completion, treatment initiation, and clinical control will be derived from the nested cohort of screen positive individuals and will be summarised and analysed as site period proportions. Missing data will be handled using multiple imputation with additional sensitivity analyses to evaluate the robustness of findings. If individual level data are pooled across sites with fixed per site samples, design weights proportional to the site population of eligible invitees will be used to account for unequal selection probabilities (See Supplementary File 1).

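### Follow-up completion and treatment initiation are taken from all screen-positives, without separating people already diagnosed or treated

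*Protocol article*

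**What the plan says.** **Who is invited.** Under Phase III the only stated criteria are overseas birth and age: "people from these communities who were born overseas and are 40 years or older will be registered and invited for the service".

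**Reach.** Under Outcomes of model implementation, the primary impact outcome is "the proportion of eligible CALD adults completing hypertension and/or diabetes screening", and "Reach will be calculated as the number screened divided by the number invited within each site and period".

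**The cohort behind the secondary outcomes.** The same section states that "individuals who screen positive during each measurement period will form a nested cohort for follow up". The Data analysis plan for the main model derives follow-up completion, treatment initiation and clinical control from this cohort, as site-period proportions.

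**What counts as success.** Table 2 defines the follow-up rate as the percentage "of screen-positive individuals who receive timely confirmatory diagnosis and/or treatment". Treatment initiation is named as a secondary outcome, but the article gives it no operational definition. Table 2 sets control among people who have been diagnosed, which is a different base from the screen-positive cohort used in the analysis plan.

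**Where prior disease appears.** It appears only as a model covariate: "Key participant characteristics including age, sex, region of birth, education, primary language, and baseline comorbidities will be included as covariates".

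Supplementary File 1, to which the outcome and analysis sections refer, is not shown.

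**The concern.** The project's stated aim is screening, and starting treatment in those diagnosed. A person already on treatment cannot start it, and a person already diagnosed needs no confirmatory diagnosis. If such a person has a high reading, the stated rules still put that person in the denominator, and the Table 2 definition can count the existing diagnosis or treatment as a success.

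Two things are at stake. First, the reported proportions would mix what the model of care achieved with care that was there before it. Second, the Difference-in-Differences contrast removes a mix of known and new cases only while that mix is stable. If the programme changes attendance differently in the two groups, the contrast moves although nobody's care has changed. Adjusting for comorbidities changes neither who is in the denominator nor what counts as an event.

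**Working it through.** **Inputs from the protocol** (Cluster size and number of expected participants): hypertension prevalence 34%; awareness, from the statement that "only one in two people detected to have hypertension are aware of their condition", 50%; screening target 50% to 70%.

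**Plan's own figures.** The plan gives no figure for the make-up of the screen-positive cohort. The sample size built on the 50% to 70% target does reproduce. Unpooled variance with two-sided 5% and 80% power gives (1.96 + 0.842)² × (0.25 + 0.21) / 0.20² = 90.3, so 91 per group and 182 in total. The design effect is 1 + 99 × 0.02 = 2.98, and 182 × 2.98 = 542.4 (stated: about 543).

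**Step 1: known cases among invitees.** 0.34 × 0.50 = 0.17 have known hypertension. The other 0.34 − 0.17 = 0.17 have it undiagnosed.

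**Step 2: known cases among blood-pressure screen-positives.** Assume equal attendance, and let c be the share of known cases whose pressure is controlled, so that they do not screen positive. The known share is s = 0.17(1 − c) / [0.17(1 − c) + 0.17] = (1 − c)/(2 − c).

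| c (assumed) | s |
|---|---|
| 0 | 50% |
| 0.5 | 33% |
| 0.7 | 23% |

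**Step 3: effect on the observed proportion.** Assume that 50% of new cases truly start treatment.
- Known cases all counted as treated, s + (1 − s) × 0.5: 67% at s = 1/3 and 75% at s = 1/2.
- Known cases all counted as not initiating, (1 − s) × 0.5: 33% and 25%.

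The same care can therefore be reported as anything from 25% to 75%, depending on a rule that the article does not state. In either case, if the status of known cases does not change between periods, a true change Δ in new cases appears as (1 − s)Δ, which is two-thirds to one-half of its size.

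**Step 4: movement from case mix alone.** This is a different scenario and is not to be added to Step 2. Assume that all known cases are seen in both periods and are uncontrolled, that 90% of known and 50% of new cases are treated, and that overall screening goes from 50% to 70%. Screening among people without known hypertension is then (0.50 − 0.17)/0.83 = 0.398 at baseline and (0.70 − 0.17)/0.83 = 0.639 at follow-up.
- Baseline, per 100 invitees: (17 × 0.9 + 17 × 0.398 × 0.5) / (17 + 17 × 0.398) = 78.6%.
- Follow-up: (17 × 0.9 + 17 × 0.639 × 0.5) / (17 + 17 × 0.639) = 74.4%.

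The treated proportion falls by 4.2 points with no change in anyone's care. Under equal attendance in both periods this shift is zero.

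**The case against.** **The article leaves the point open.** Initiation ordinarily means a new start, no sentence says that treated people count as successes, and Supplementary File 1 may settle it. This stands for the treatment-initiation event. It does not stand for the cohort or the follow-up rate: the article fixes both, and neither sets known cases apart.

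**Known cases belong under control.** Bringing a known but uncontrolled person under control is a legitimate result. This stands, and it is why known cases should be kept as a stratum and not discarded.

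**The magnitudes rest on assumptions.** Attendance, control and treatment rates are not in the protocol. This stands, and it is why ranges are given.

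**A stronger reading about Reach.** A reader might infer that known hypertensives also dilute Reach, cap it at 1 − 0.17 = 83%, and raise the uptake needed for the 70% target to 0.70/0.83 = 84%. The protocol does not support this, for four reasons.
- Reach counts hypertension and/or diabetes screening, so a person with known hypertension can still complete it through diabetes screening.
- The direction depends on attendance, which is not given. Suppose people without known hypertension go from 50% to 70%. Reach then rises by 16.6 points if known cases never attend (0.83 × 20), by 20 points if they respond alike, and by 23.4 points if they go from 50% to 90% (0.83 × 20 + 0.17 × 40).
- Even the first case needs about 828 people by the plan's own method (139 per group, 278 × 2.98), which is below the planned 1,200.
- The programme aims to produce diagnoses. Removing people by prior diagnosis at follow-up would condition the primary denominator on something that the intervention changes.

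**Conclusion.** The point holds for the secondary outcomes. As written, follow-up completion and treatment initiation are calculated on a cohort that mixes new cases with people already diagnosed or treated, and the covariate adjustment does not repair this. On the plan's 34% and one-in-two figures, known cases would be about a third to a half of blood-pressure screen-positives. That range assumes equal attendance, between none and half of known cases controlled, and positive readings in all undiagnosed cases who attend. With better control the share is lower (23% at 70% controlled). Diabetes screen-positives are not included in these figures. A case-mix shift of about 4 points is possible under the labelled assumptions, but the protocol does not imply it.

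The point does not extend to the definition of primary Reach, and it is not a power problem. It concerns what the secondary proportions mean, and it should be settled before baseline data are collected.

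**What to change.** 1. Record prior diagnosis of hypertension and of diabetes, and current treatment for each, at registration. Use the same question and reference date in both arms and both periods.
2. In the outcomes section, Table 2 and the analysis plan, restrict follow-up completion to screen-positives with no prior diagnosis of that condition, and treatment initiation to those untreated for it at screening.
3. Report previously diagnosed people as a separate stratum, for example for control, and use the same base for control in Table 2 and in the analysis plan.
4. Keep primary Reach as screened divided by invited. Add Reach among people without a known diagnosis as a supportive analysis only, noting that diagnosis status at follow-up can be changed by the intervention.

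These changes concern analysis denominators only, not who is offered the service or how anyone is managed.

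**Cost.** One registration item, a change of definitions, some self-report error and a smaller secondary-outcome cohort. Under the equal-attendance assumption, the restriction to people without a prior diagnosis removes a third to a half of blood-pressure screen-positives. Per 100 invitees it leaves about 100 × 0.17 × 0.50 = 8.5 new cases at 50% screening and 100 × 0.17 × 0.70 = 11.9 at 70%, so site-period proportions will be imprecise and should be read accordingly.

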#### Planned activities that will be implemented in Phase III:

##### Development of a structured training curriculum and training manual

The project implementers will develop structured training modules based on the intervention packages requirements developed in Phase II and in consultation with other stakeholders. The training manuals will be contextualized to the practice change needs based on the preliminary findings and the co-developed multi-packaged model of care. The training sessions will be conducted using interactive sessions and practical demonstrations. A pre- and post-training assessment will be provided to the trainees to assess the practice and knowledge changes acquired from the training modules and identify the need for re-training before initiation of the project implementation process.

##### Capacity building for project implementers

The project steering committee (comprising of a multidisciplinary team of project implementers from different implementing sites) will provide a comprehensive training to the relevant stakeholders including the health workers who are directly involved in providing health care services for the selected NCDs. If this is not possible, the training will be provided by the project advisory members using online training platforms. The training will be provided with a combination of four to five interactive sessions, and didactic lectures to enhance the adoption of the multi-packaged interventions. The healthcare professionals and other stakeholders undergoing training will be assessed for knowledge and practice change using a pre-developed assessment module. A score of > 80% in the training assessment will be considered adequate and, if the score is < 80%, a re-training session will be provided [22].

##### Implementation of the multi-packaged model of care

Baseline data will be collected, and the model of care will be implemented in those settings in collaboration with different stakeholders, after completion of the trainings. The process of model implementation to enhance access to and utilization of health care services for hypertension and diabetes mellitus screening, and initiation of treatment for those diagnosed among CALD communities and other secondary objectives will be recorded. In addition, any challenges experienced in the adoption of the interventions will be documented and communicated for concerned bodies including the project implementing agencies.

##### Identification of model implementation co-ordinators and facilitators

We will be selecting one or more model implementation coordinators to run the overall implementation process. These individuals will be selected based on their experience and leadership qualities to promote good governance, accountability, and high-quality services. In addition, one facilitator will be selected at each implementing site. These facilitators will be drawn from experienced clinical leaders, health managers, and/or frontline staff members. These facilitators will be tasked to ensure the adoption of the multi-packaged interventions of the model of care being implemented in their respective settings. In addition, they will play a key role in guiding the model implementation process, monitoring progress, ensuring the quality and consistency of service delivery, facilitate timely data collection, and lead regular performance reviews. They will also assess whether interim or re-training is necessary at each site. Re-training will be scheduled if non-compliance with the protocols of the multi-packaged interventions is noted at a particular site as assessed by the implementation protocol checklist. If non-compliance is persistent, then it will be communicated to the project advisory group. They will also support in problem-solving at the facility level, encourage the use of evidence for decision-making, and ensure that reporting mechanisms are transparent and actionable. The project implementation advisory group will take the responsibility to identify these facilitators for each setting in collaboration with the site project implementing agencies. Subsequently, the project advisory group will conduct a process evaluation, and in-depth interviews will be carried out to explore the issues and challenges encountered in the implementation of these interventions, as described below.

